**Method:**

This is a single blinded, randomized sham-controlled trial, targeting at young healthy adults aging from 18 to 24 years old. Forty eligible volunteers will be recruited and randomly divided into active and sham rTMS group. All subjects will take a set of neuropsychological and biological assessments and MRI scanning before and right after the intervention. During the interventional period, 12-session stimulations will be performed in 4 weeks with three sessions per week. The primary outcome will detect the difference of Chinese 14-item perceived stress scales between active and sham rTMS groups after intervention. Secondary outcomes will examine the differences of other affective measurements, level of cortisol, and MRI-derived neural functional measures between the two groups after intervention.

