### Inclusion procedure

Before the beginning of the intervention, individuals who are interested in participation are invited for an appointment to provide more information. If they are willing to participate, informed consent will be signed following the guidance from an independent researcher and the participant will be screened by the inclusion and exclusion criteria. If the subject meets all the inclusion criteria and none of the exclusion criteria, the subject will be included in the study. After inclusion, and before the randomization and allocation, the descriptive data should be collected carefully to get the general information of participants. The basic data are composed of age; gender; race; employment; height; weight; body mass index (BMI); blood pressure; educational level; history of diseases; medication; abuse of smoke, drug, or alcohol; and the habit of exercise. Furthermore, all participants will be assessed by five scales: PSS-14, Depression Anxiety Stress Scale (DASS), Chinese Affective Scale (CAS), Montreal Cognitive Assessment (MoCA), and Test of Nonverbal Intelligence, Third edition (TONI-3). MOCA and TONI-3 are tested as the control factors to ensure there is no significant difference in cognition between the active and sham groups. Biological indicators including sample of serum cortisol will also be collected. Moreover, the anatomy and functions of brain will be scanned by magnetic resonance imaging.

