### Primary outcome measurement

The primary outcome is the change in perceived stress levels, which is measured by Chinese 14-item perceived stress scales (PSS-14) [28]. The PSS consists of 14 items (7 positive items and 7 negative items) and is a widely used psychological scale to observe the perception of stress in different situation [29]. Participants are required to complete all questions that indicated their perceived stress level within the past several months. Each item is rated on a 5-point scale ranging from 0 (means never) to 4 (means very often), whereas the higher scores indicate higher stress level [30, 31]. Data will be collected at the baseline assessment and the end of intervention (4 weeks after randomization). The mean scores will be calculated for the subsequent statistical analyses.

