### Sample size calculation

We aim to investigate the efficacy of the technique of rTMS for improving cognitive emotional control in high-level perceived stress individuals. Since there are no studies of the rTMS efficacy on perceived stress, we have referred to related literature that investigated the effect of rTMS on depression [37], and the sample size estimation was based on the improvement of Hamilton Depression Rating scale (HDRS-17) scores. According to a previous study [37], the mean and its SD of HDRS-17 scores after a 4-month active rTMS intervention (10 subjects included) for treatment-resistant depression were 7.70 and 4.34, respectively, whereas they were 12.29 and 4.50 in the sham rTMS group (7 subjects included), respectively, resulting an effect size (Cohen’s *D*) of 1.038. Referencing from these, a sample size of 32 participants was calculated to sufficiently detect the target effect size (1.04) with a type I error of 5% (*α* = 0.05) and 80% power (*β* = 0.20) by Gpower V.3.1.9.2 software. However, to overcome a dropout rate of 20%, we increased the number of enrollments and finally 40 participants will be allocated randomly into the active and sham stimulation groups with 20 participants in each group for the completion of this trial.

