### Statistical analysis

All statistical analyses of non-imaging data will be conducted using SPSS Version 25 by an independent statistician who is blinded to the labeling of active and sham groups. The statistical significance level of test is established at 0.05, two-tailed. In the process of data analysis, continuous variables will be represented using mean, standard deviation, maximum or minimum according to the statistical distribution, and the categorical data will be presented by percentage. To verify the efficacy of our intervention, comparison of all outcomes which are categorized as continuous variable and shown in mean scores will be included into analysis by independent sample t test or non-parametric test (Mann-Whitney *U* test). Moreover, both analysis within group and between groups after 4-week intervention will be carried to observe the difference of these two interventional methods. If necessary, logistic regression, general linear correlation or regression will be taken into consideration between different types of outcomes. Similarly, according to the type and distribution of variables, the comparison of basic data between the active group and sham rTMS group will be performed using Student’s *t* test, chi-squared test, or nonparametric test. Furthermore, the participants who drop out during the intervention period will not be excluded due to the principle of Intention to treat (ITT) and the missing data will be replaced by last observation carried forward rules.

The hypothesis of this trial is that the active stimulation group shows greater changes than the sham stimulation group. Therefore, the main analysis is the comparison of changes between groups, measured at baseline and at the end of intervention. If significant differences are observed after intervention and no significant difference is observed at the baseline, we may conclude the efficacy of rTMS to individuals with high level of perceived stress.

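### The efficacy rule depends on a non-significant baseline test and does not fix whether PSS-14 is compared as change or as end-of-intervention score

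*Protocol article*

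**What the plan says.** All of this is in the protocol article.

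- **Statistical analysis, main analysis:** "the main analysis is the comparison of changes between groups, measured at baseline and at the end of intervention".
- **Statistical analysis, decision rule (the next sentence):** "If significant differences are observed after intervention and no significant difference is observed at the baseline, we may conclude the efficacy" of rTMS. The sentence names no outcome.
- **Primary outcome measurement:** "The primary outcome is the change in perceived stress levels", measured by PSS-14.
- **Abstract, Method:** "The primary outcome will detect the difference of Chinese 14-item perceived stress scales between active and sham rTMS groups after intervention".
- **Inclusion procedure:** "MOCA and TONI-3 are tested as the control factors to ensure there is no significant difference in cognition between the active and sham groups".
- **Test level:** "The statistical significance level of test is established at 0.05, two-tailed".

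The Sample size calculation section takes its effect size from end-of-treatment means in an earlier depression trial, and plans 32 evaluable participants, enrolled as 40 to allow for 20% dropout.

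**The concern.** Two separate faults meet in the decision rule.

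The first is the baseline condition. Allocation is by random permuted blocks, so any baseline difference between arms is due to chance. A significant baseline test does not show that the trial is invalid, and a non-significant one does not show that the arms are balanced enough to ignore baseline. The rule therefore discards some sound trials and gives false comfort in others. The planned tests of MoCA and TONI-3 rest on the same reasoning, although they are not part of the efficacy rule.

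The second is the contrast. A comparison of changes and a comparison of end-of-intervention scores are different tests with different power, and they can give different answers in the same data. Consecutive sentences of the plan point to different ones. If they disagree when the data arrive, the text does not say which one decides. The rule also omits to say that PSS-14 is the outcome to which it applies.

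**Working it through.** **Inputs from the protocol article.** Two-sided alpha 0.05; power 80%; end-of-treatment means (SD) of 7.70 (4.34) active and 12.29 (4.50) sham; target effect 1.04; 32 evaluable (16 per arm); 40 enrolled (20 per arm).

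**Assumed.** The baseline-to-end correlation r of PSS-14 is not given, so I use 0.3, 0.5 and 0.7. Scores are taken as bivariate normal with equal SD.

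**Step 1: the plan's own figures.** d = (12.29 − 7.70) / √[(4.34² + 4.50²)/2] = 4.59 / 4.42 = 1.038. With 16 per arm the noncentrality is 1.04 × √(16/2) = 2.94 on 30 df; two-sided power is 0.812. 32 / 0.8 = 40. The sample size reproduces and is not in dispute.

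**Step 2: the effect size that each contrast sees.** Taking d = 1.04 on the end-of-intervention SD:

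- end score: d, whatever r is
- change: d / √[2(1 − r)] = 0.88, 1.04, 1.34 for r = 0.3, 0.5, 0.7
- baseline-adjusted (ANCOVA): d / √(1 − r²) = 1.09, 1.20, 1.46

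**Step 3: power at d = 1.04, 16 per arm** (simulation, 100,000 trials per setting, each test at two-sided 0.05). Gated means that the baseline t test must also be non-significant.

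| r | End score | End score, gated | Change | Change, gated | ANCOVA, no gate |
|---|---|---|---|---|---|
| 0.3 | 0.810 | 0.772 | 0.673 | 0.644 | 0.834 |
| 0.5 | 0.811 | 0.777 | 0.812 | 0.777 | 0.898 |
| 0.7 | 0.813 | 0.782 | 0.957 | 0.911 | 0.974 |

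The gate is passed in 95% of trials whatever the treatment effect, so it blocks 5%. With 20 per arm and r from 0.3 to 0.7, it takes end-score power from 0.89 to 0.85-0.86.

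**Step 4: how often the two contrasts disagree** (no gate, d = 1.04, 16 per arm). P(disagree) = 2 × P(either significant) − P(end) − P(change).

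- r = 0.3: 2 × 0.8740 − 0.8101 − 0.6732 = 0.265
- r = 0.5: 2 × 0.9223 − 0.8113 − 0.8119 = 0.221
- r = 0.7: 2 × 0.9800 − 0.8129 − 0.9566 = 0.191

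**Step 5: type I error, 16 per arm.**

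| r | End score, gated | Change, gated | Either, gated | Either, no gate | ANCOVA, no gate |
|---|---|---|---|---|---|
| 0.3 | 0.045 | 0.038 | 0.071 | 0.088 | 0.049 |
| 0.5 | 0.040 | 0.040 | 0.072 | 0.089 | 0.049 |
| 0.7 | 0.034 | 0.043 | 0.071 | 0.092 | 0.050 |

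Results with 20 per arm are nearly the same (either, gated: 0.072-0.073).

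**Step 6: what the gate lets through.** With 20 per arm, a baseline gap of 0.5 SD gives t = 0.5 × √(20/2) = 1.58 on 38 df, p = 0.12, so it passes. If r = 0.5, the unadjusted end-score test then has a conditional type I error of about 0.09.

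**The case against.** The strongest reply is that the rule is safe. Adding a second condition can only make a positive conclusion rarer, and for one fixed PSS-14 contrast its type I error is about 3-5%. That stands: the gate alone costs power and does not inflate error. The power loss is also modest, 3 to 4 points for the end score, and if all 40 participants contributed full data the gated power would still be about 0.85.

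It can also be said that the plan declares one main analysis, the comparison of changes, that the outcome definition agrees with it, and that an abstract is condensed. The decision sentence follows directly and might be read as referring to changes. This is a fair defence, but incomplete: a separate condition on baseline makes little sense for a change score, so the more natural reading is a comparison of end scores. The text leaves both open.

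Four stronger readings are tempting, and the document does not support them.

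- *No primary outcome.* PSS-14 is named primary in the abstract, in Study design and in its own section. Only the decision sentence omits it.
- *Either contrast may be chosen, giving about 9% error.* Nothing says that either suffices, and 9% ignores the gate. With the gate the figure is about 7%.
- *The gate covers every baseline variable and so blocks a large share of trials.* No such extension is stated. MoCA and TONI-3 are called control factors and are not conditions for efficacy.
- *Within-group tests can establish efficacy.* The tests named for verifying efficacy are between-group. Within-group analysis is mentioned afterwards, alongside between-group analysis, and the hypothesis is a between-group one.

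**Conclusion.** The concern holds in limited form. The baseline condition is stated outright and is uninformative under randomisation. It blocks about 5% of sound trials, takes end-score power at the plan's own effect and evaluable number from about 0.81 to 0.77-0.78, and leaves non-significant imbalances unadjusted.

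The switch between change and end score is real. At d = 1.04 with 16 per arm the two tests disagree in about 19 to 27% of trials, and change-score power runs from 0.67 to 0.96 against a steady 0.81 for end scores. These ranges rest on the assumed correlation of 0.3 to 0.7 and on normality.

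A reader might infer that the rule is an inflated test. It is not, for a single fixed PSS-14 contrast; error exceeds 5% (about 7%) only if either contrast could count, which the text neither grants nor rules out. The missing PSS-14 label in the rule is a gap in wording.

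**What to change.** In Statistical analysis, replace the decision sentence with: *Efficacy will be concluded only if the between-group difference in PSS-14 at the end of intervention, adjusted for baseline PSS-14 by analysis of covariance, is significant at the two-sided 0.05 level.*

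Then:

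- delete the condition on baseline significance, and report baseline data, including MoCA and TONI-3, descriptively
- use the same description of the primary comparison in the abstract, in Primary outcome measurement and in Statistical analysis
- state that secondary outcomes and within-group results are supportive and cannot by themselves establish efficacy.

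This holds type I error at about 5% and gives power of about 0.83 to 0.97 with 16 per arm for correlations of 0.3 to 0.7, with no extra participants or data. It is more than a wording change, because the planned two-sample t test or Mann-Whitney test gives way to a regression model. Recruitment began in June 2020, so it needs a formal amendment submitted to the ethics committee and settled before unblinding.

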### Secondary outcome measurements

The secondary outcome measurement includes 2 scales of psychological domains, serum cortisol and neuroimaging data. Data will be collected at the baseline assessment and the end of intervention (4 weeks after randomization). Specifically, the mean scores of the psychological measures, the gray matter density in bilateral DLPFC, the functional connectivity with the DLPFC as seed, and task activation will be calculated as the secondary outcomes. Detailed analyses are stated in the section of “Statistical analysis”.

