In addition, the left and right side of DLPFC will be set as the seed regions for the analysis of the structural and functional MRI data to examine the longitudinal neural changes and to explore the relationship between the brain plasticity and perceived stress caused by the stimulation. Specifically, the gray matter density in bilateral DLPFC, the functional connectivity with the DLPFC as seed, and task activation will be calculated using statistical parametric mapping software (SPM12, Welcome Department of Cognitive Neurology, London, UK, http://www.fil.ion.ucl.ac.uk/spm/). A two-factor repeated measures ANOVA (group factor for active and sham groups, and two longitudinal measures at baseline and after intervention) will be conducted on the gray matter density, functional connectivity, and the task activation separately. Further correlational analyses will be performed between the imaging and the psychological and biological measures to explore the relationship between brain and perceived stress.

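### For region-level imaging outcomes, the two-visit group-by-time ANOVA is valid but usually less precise than adjusting for the baseline scan already collected (low priority)

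*Protocol article*

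**What the plan says.** Under Statistical analysis, the article specifies the imaging model as "A two-factor repeated measures ANOVA (group factor for active and sham groups, and two longitudinal measures at baseline and after intervention"), and says that it "will be conducted on the gray matter density, functional connectivity, and the task activation separately". No baseline covariate is included. SPM12 is named as the software.

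Under Secondary outcome measurements, these measures are secondary: "the functional connectivity with the DLPFC as seed, and task activation will be calculated as the secondary outcomes".

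The baseline scan exists for this purpose. The abstract plans "MRI scanning before and right after the intervention", and the Inclusion procedure and Randomization sections place the baseline evaluation ahead of allocation.

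Statistical analysis also states the target of inference: "the main analysis is the comparison of changes between groups, measured at baseline and at the end of intervention". Regression is mentioned there only as an option for relating different types of outcome to each other, so no baseline-adjusted comparison is planned for any outcome.

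**The concern.** The model is a stated choice, and in a two-visit design it reduces to a comparison of change scores. A change score subtracts the whole baseline value, whatever the correlation between visits. When that correlation is moderate, this adds noise that a fitted baseline slope would remove.

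The trial expects 16 to 20 usable scan pairs per arm, and the effect on brain function is a stated secondary aim. Since the baseline scan is taken before allocation, it is a legitimate covariate and costs nothing further to acquire. What is at stake is power and the width of confidence intervals for the region-level imaging contrasts. The validity of the test is not in question.

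**Working it through.** **1. The plan's own figure.** The article gives no sample size for imaging. Its only calculation, under Sample size calculation, uses a depression scale.
- Effect size: d = (12.29 − 7.70)/√((4.34² + 4.50²)/2) = 1.038.
- A two-sided t test at 0.05 needs 16 per arm (power 81.2%; 15 per arm gives 78.5%), so 32 evaluable.
- Dropout: 32/(1 − 0.20) = 40 randomised.

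The stated 32 and 40 are reproduced, and nothing below changes them. They supply the sample sizes used here: 16 per arm (N = 32) and 20 per arm (N = 40).

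**2. Assumptions not in the article.** Rho, the correlation between baseline and post-intervention values, is not given, so a range is shown. The effect of 0.7 post-intervention SD is illustrative. Equal SDs at both visits are assumed. The level, "The statistical significance level of test is established at 0.05, two-tailed", is stated in the paragraph that opens with non-imaging data and is carried over to imaging.

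**3. The interaction is a change-score test.** On a generated dataset with 16 per arm, the interaction F was 1.2889 and the squared t on change was 1.2889.

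**4. Variance of the two contrasts.** In units of the single-visit variance:
- change score: 2(1 − rho)
- ANCOVA, large sample: 1 − rho²
- ratio of ANCOVA to change: (1 + rho)/2

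Estimating the slope in a small trial multiplies the ANCOVA variance by 1 + 1/(N − 4), which is 1.036 at N = 32 and 1.028 at N = 40.

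| rho | ratio, N = 32 | ratio, N = 40 |
|---|---|---|
| 0.3 | 0.67 | 0.67 |
| 0.5 | 0.78 | 0.77 |
| 0.7 | 0.88 | 0.87 |
| 0.9 | 0.98 | 0.98 |
| 0.95 | 1.01 | 1.00 |

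**5. Break-even.** Setting (1 + rho)/2 × (N − 3)/(N − 4) = 1 gives rho = 1 − 2/(N − 3). That is 1 − 2/29 = 0.93 at N = 32 and 1 − 2/37 = 0.95 at N = 40. Above these values ANCOVA is slightly the less precise of the two.

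**6. Power, 0.7 SD effect, noncentral t.** The standardised effect is 0.7/√(2(1 − rho)) on N − 2 df for change, and 0.7/√((1 − rho²)(1 + 1/(N − 4))) on N − 3 df for ANCOVA. At rho 0.5 and N = 32 these are 0.700 and 0.794.

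| rho | 16 per arm: change → ANCOVA | 20 per arm: change → ANCOVA |
|---|---|---|
| 0.3 | 37% → 50% | 45% → 61% |
| 0.5 | 48% → 58% | 58% → 69% |
| 0.7 | 70% → 75% | 80% → 85% |
| 0.9 | 99% → 99% | over 99% for both |

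**7. Simulation check.** With 20,000 runs per setting, 16 per arm and a 0.8 SD effect, power was 46% against 61% (rho 0.3), 59% against 70% (0.5) and 80% against 85% (0.7). The variance ratios were 0.67, 0.79 and 0.89, and 1.02 at rho 0.95, in line with the formulas.

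**The case against.** The strongest reply is that nothing here is an error: the planned model is standard, valid and unbiased under randomisation. That stands, and it makes this an efficiency improvement. Four stronger readings are tempting, and the article does not support them.

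- *That conclusions might rest on the group or time main effect.* The article does not name the decisive ANOVA term for imaging. It does, however, state a hypothesis of greater change in the active arm and make the between-group comparison of changes the main analysis. In this design that is the interaction. Naming the term is detail that a condensed article can leave to the full plan.
- *That ANCOVA is never less precise.* This is a large-sample result. At this sample size it fails above a rho of about 0.93 to 0.95, although the loss there is about 1 to 2% in variance.
- *That chance baseline imbalance biases the change-score test.* Over randomisation it does not. Conditional on an imbalance, it is the same precision loss seen from another angle and should not be counted twice.
- *That every imaging analysis should change.* Only gray matter density in bilateral DLPFC reads clearly as a regional value. The article does not say whether connectivity and task activation are extracted as regional values or analysed as maps, and for voxelwise maps the planned model is reasonable.

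It is also fair that the loss is not established for these measures. Rho is unknown and may differ between the three. Under the article's only effect size, 1.04, which is not an imaging figure, rho 0.7 with 16 per arm gives 95.7% against 97.4%, which hardly matters.

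**Conclusion.** The point holds as a low-priority efficiency improvement for region-level imaging values. With equal variances at the two visits, baseline adjustment cuts the variance of the active-sham contrast by about 33%, 22% and 12% at rho 0.3, 0.5 and 0.7 with 32 participants (one minus the ratios in the table). For an assumed 0.7 SD effect this is worth about 13, 10 and 5 percentage points of power. At rho 0.9 the variance saving is about 2% and there is no useful gain; beyond 0.93 to 0.95 the comparison reverses trivially.

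The size therefore depends on a correlation and an effect that the article does not give. The planned interaction test remains valid. The sample size and the primary perceived-stress conclusion are unaffected. The imaging outcomes are secondary and the abstract describes the protocol as exploratory, which keeps the priority low.

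**What to change.** For region-level imaging values (gray matter density in left and right DLPFC, and connectivity or task activation wherever regional values are extracted), replace the repeated-measures ANOVA with an ANCOVA. Model the post-intervention value on group, with the same measure's baseline value as covariate, and report the adjusted active-sham difference with its 95% CI. The group-by-time ANOVA can stay as a supportive analysis.

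For voxelwise SPM12 maps, keep the planned model and read it on the group-by-time interaction, consistent with the comparison of changes already stated as the main analysis.

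The cost is a change of analysis wording, one residual degree of freedom per model, and a trivial loss of precision if rho turns out to exceed about 0.95. No new data and no change in sample size are needed.
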